## Abstract

**Background:**

If conservative treatment for chronic plantar fasciitis fails, often a corticosteroid injection is given. Corticosteroid injection gives temporarily pain reduction, but no healing. Blood platelets initiate the natural healing rate. GPS^® ^gives an eightfold concentrate platelets of patients own blood. Injection of these platelets in the attachment of the fascia to the os calcis might induce a healing rate.

**Methods and design:**

A randomized controlled multi centre trial will be performed. The study population consists of 120 patients of 18 years and older. Patients with chronic plantar fasciitis will be allocated randomly to have a steroid injection or an autologous platelet concentrate injections. Data will be collected before the procedure, 4,8,12,26 weeks and 1 year after the procedure.

The main outcome measures of this study are pain and function measured with questionnaires.

**Conclusion:**

Recent literature show positive effects for the treatment of tendinosis with autologous platelet injections. The forthcoming trial will compare treatment for chronic plantar fasciitis with a steroid injection versus an autologous platelet injection. Our results will be published as soon as they become available.

**Trial Registration:**

Trial registration number: http://www.clinicaltrials.gov NCT00758641.

PRP is promoted as an ideal autologous biological blood-derived product, which can be exogenously applied to various tissues where it releases high concentrations of platelet derived growth factors that enhance wound healing, bone healing and also tendon healing. In addition PRP possesses antimicrobial properties that may contribute to the prevention of infections [17]. When platelets become activated, growth factors are released and initiate the body's natural healing response.

We will evaluating the effects of PRP injections on "self-reported function and pain" in a double-blind randomized trial.

## Methods and design

### Study design

Randomization will be performed after patients are deemed eligible and have provided informed consent. Patients will be randomly allocated to the concentrated autologous platelet group (PRP group) or to the corticosteroid group (control group). A computer using block randomisation of 10 patients will be used to create a randomization schedule. Treatment assignments (placed in sequentially numbered opaque envelopes) will be assigned by the trial managers (WL, HS, HH, TG) who will also arrange the facilities needed for the procedure.

All patients with a plantar fasciitis who are admitted to one of the participating hospitals and meet the inclusion criteria are asked to join the study.

Plantar fasciitis was defined as pain at the point of the fascia plantaris origin at direct palpation. All affected patients were screened with X-ray of the calcaneus for bony abnormalities and to difentiate for subtalar arthritis. Sonography and MRI were not used standardly.

The Medical Ethical Committee of The Netherlands approved the study design, procedures and informed consent.

Trial registration number: http://www.clinicaltrials.gov NCT00758641.

### Study population

The study will be conducted at the Orthopaedic Departments of the HAGA Ziekenhuis Den Haag, St. Antonius Ziekenhuis Nieuwegein, Diaconessenhuis Leiden and St. Elisabeth Ziekenhuis Tilburg between November 2008 and December 2010. Authors JP and TG will be responsible for the data and safety monitoring. Inclusion criteria: patients aged > 18 years, with plantar fasciitis (6-12 months duration), who failed conservative treatment are included. They have to be able to understand the informed consent and have a VAS pain score in the morning by first steps higher as 5 (0-10 scale).

Patients will be excluded from the study when they received local steroid injections within 6 months, physical/occupational therapies within 4 weeks, or non-steroidal anti-inflammatory within 1 week prior to randomization. Also patients will be excluded with the inability to fulfil follow-up criteria, significant cardiovascular, renal or hepatic disease, pregnancy, (local) malignancy, history of amenia (hemoglobin < 5.0), previous surgery for plantar fasciitis, active bilateral plantar fasciitis, diagnosis of vascular insufficiency or neuropathy related to heel pain, hypothyroidism and diabetics.

### Intervention

#### Platelet Concentrate Preparation

Fifty-five milliliters whole blood is collected from the uninvolved arm into a 60-mL syringe that contained 5 mL sodium citrate. A peripheral complete blood count is also collected at the time of the initial blood draw. The blood is then prepared according to the GPS System instructions (Cell Factor Technologies, Warsaw, Ind). This device is a desktop-size centrifuge with disposable cylinders for the blood approximately 0.05cc Platelet concentrate is obtained for each patient.

Autologous platelet concentrate contains concentrated white blood cells and platelets that are suspended in plasma. Since an acidic anticoagulant is introduced to the whole blood used to produce the platelet concentrate, the platelet concentrate must be buffered to increase the pH to normal physiologic levels. This is accomplished with 8.4% sodium bicarbonate solution added at a ratio 0.05cc of sodium bicarbonate solution to 1 cc of platelet concentrate.

The resulting buffered platelet concentrate contains approximately a 6 to 8 times concentration of platelets compared to baseline whole blood. No activating agent is used. The total time from blood draw to injection in the patients is about 30 minutes. No specialized equipment, other than the GPS machine, is required.

#### Injection Technique

Initially, bupivacaine is infiltrated into the skin and subcutaneous tissue of both groups as a local field block. Approximately 0.05cc is also injected directly into the area of maximum tenderness. Then, either 5 to 6 cc platelet concentrate or 5 to 6cc corticosteroid is injected using a 22-g needle into the plantar fasciitis using a peppering technique. This technique involved a single skin portal and then 5 penetrations of the fascia.

#### Post-procedure Protocol

Immediately after the injection, the patient is kept in sitting position without moving the foot for 15 minutes. Patients will go to the physiotherapist to obtain stretching exercises. Patients are sent home with instructions to limit their use of the feet for approximately 48 hours and use hydrocodone or acetaminophen for pain. The use of nonsteroidal medication is prohibited. After 48 hours, patients are given a standardized stretching protocol to follow for 2 weeks. A formal strengthening program is initiated after this stretching. At 4 weeks after the procedure, patients are allowed to proceed with normal sporting or recreational activities as tolerated. Any type of foot orthoses will not be allowed.

#### The corticosteroid

The type of steroid that is used during the study is kenacort 40 mg/ml triamcinolon acetonide.

### Study parameters/endpoints

#### Main study pain

Pain will be measured using a visual analogous scale at all time points. The VAS score of the Foot Function Index will be used.

The score records the patient's reported pain using a scale of 0-10, where 0 is pain-free and 10 is the worst pain imaginable. The scale will be a 10 centimeter line beginning with 0 and ending with 10, the score will be marked at the point on the line that corresponds with the patient response.

Each patient randomly assigned to a treatment and with at least one non-missing pre- and post-baseline measurement, will be classified at each visit, as either a treatment success or failure. Patients with a score reduction of 25% compared to baseline, did not require pain medication beyond the protocol defined allowable period, and did not require escape therapy will be considered a treatment success.

The absolute change from baseline to endpoint means the baseline value is subtracted from the endpoint value. Percent change is defined as the absolute change multiplied by 100 divided by the baseline value. For patients whose pain improves, these values will be less than zero.

The treatment is defined as successful if the pain reduction after 6 months is over 25%. If the patient is lost to follow-up, the last measurement will be carried forward. If the patient has obtained a different treatment, the subject is classified as unsuccessful.

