#### Follow up

All patients will be followed up at 4, 8, 12, 26 and 52 weeks. All patients will complete AOFAS and VAS scores at all follow up moments

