#### Determination of sample size

This study has two main parameters: number of patients with 25% pain reduction after 6 months and the average pain reduction;

Corticosteroids and stretching have a recurrence of pain after 6 months [2,25]. Previous studies with platelet rich plasma by tendonitis showed that the platelet rich plasma group has no recurrence. These results showed 63 percent success rate (VAS reduction over 25 percent after 6 months) for the platelet rich plasma group compared to 27 percent success rate for the corticosteroid group. If these percentages are comparable for plantar fasciitis 38 patients are needed in all groups to achieve a 25% pain reduction (alfa 0,05 and power 0,9).

Conservative treatment with taping or stretching shows a 30 ± 24 points decrease in VAS pain at walking [26,27]. Corticosteroid injections have shown to have comparable results [2,25]. 25% increase in pain reduction is seen as clinical relevant. To prove a difference in pain reduction of 15 ± 24 points and a α of 0,05 and a power of 0,9, 55 patients are needed in each group.

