#### Statistical analysis

This is a double blind randomized and prospective study. Patients will be randomized in equal proportions to either autologous platelet concentrate or corticosteroid injections. The primary endpoint of the trial is treatment success at 6 months. The other measurements are to measure the speed of recovery and the re-occurrence of pain.

Statistical analyses will test the null hypotheses of no differences between patients treated with autologous platelet concentrate and those treated with corticosteroid in the proportion of the protocol defined, successfully treated patients.

All tests of treatment effect will be made using a one-sided alpha level of 0.025, unless otherwise specified. Tests for the interaction between treatment and a blocking factor will be made at the alpha level of 0.10. All p-values will be rounded then quoted to 3 decimal places, unless the true p-value is less than 0.001 whereby the notation (p < .001) will be used or if the true p-value is greater than 0.999, in which case the notation (p > .999) will be used. Confidence intervals, where indicated for the difference between the two treatment groups, will be calculated at the 95% level. All data will be analyzed by a blinded researcher.

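### Carrying the last VAS forward to month 6 credits the steroid arm with relief that the protocol expects to wear off; the bias is modest at the planned loss and favours steroid

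*Protocol article*

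**What the plan says.** The Statistical analysis section of the protocol article fixes the endpoint: "The primary endpoint of the trial is treatment success at 6 months". Under Main study pain, "The treatment is defined as successful if the pain reduction after 6 months is over 25" per cent. The same section states the rule for missing data: "If the patient is lost to follow-up, the last measurement will be carried forward". One exception follows: "If the patient has obtained a different treatment, the subject is classified as unsuccessful". The visit-level definition of success also rules out pain medication beyond the allowed period and escape therapy. Only randomised patients "with at least one non-missing pre- and post-baseline measurement" are classified at all.

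The Follow up section sets the schedule: "All patients will be followed up at 4, 8, 12, 26 and 52 weeks".

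The article also describes how it expects the two arms to behave. The abstract says: "Corticosteroid injection gives temporarily pain reduction, but no healing". The sample-size section says: "Corticosteroids and stretching have a recurrence of pain after 6 months", and sets this against earlier platelet studies in tendonitis without recurrence. Background and Discussion both describe steroid benefit as short-lived and small, and the Discussion adds that relapse is frequent.

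**The concern.** Carry-forward assumes that a patient's pain does not change after the last visit attended. For the steroid arm the protocol assumes the contrary. The primary question is whether relief is still present at month 6, and the rule removes relapse from the data of those who leave before then.

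The affected group is specific: steroid patients lost at or before week 12 whose last VAS shows more than a 25% reduction and for whom no other treatment, escape therapy or excess pain medication is known. They are scored as 6-month successes. The steroid success rate is then too high and the estimated difference too small.

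The rule also treats filled-in values as if they had been observed, so the stated uncertainty is too small. This is a rule the article commits to for its primary endpoint, not a detail left to an analysis plan.

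**Working it through.** **Inputs from the article.** Success at 6 months is 63% with PRP and 27% with steroid (Determination of sample size). There are 60 patients per group, 55 needed plus an allowance for loss (Needed number of patients), so the planned loss is 5/60 = 8.3%. One-sided alpha is 0.025 (Statistical analysis), equivalent to two-sided 0.05.

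**Inputs assumed, because the article does not give them.** Steroid success at the last visit attended, e, is 50% to 90%. The alternative loss is 20%. PRP stays at 63% among leavers, in line with no recurrence. Leavers have the same true 6-month rates as completers.

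**The plan's own figures.**
- Proportions: n = [1.960·√(2·0.45·0.55) + 1.282·√(0.63·0.37 + 0.27·0.73)]² / 0.36² = 38.01. The article's 38 per group is reproduced (39 if rounded up).
- Means: n = 2·(24·3.2415/15)² = 53.8, so 54; the article's 55 is reproduced.
- Inflation: 55/(1 − 5/60) = 60.

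**Power without distortion.** Power = Φ[(difference − 1.96·se0)/se1], with se0 from the pooled rate and se1 from the separate rates. For 63% versus 27% with 60 per group, se0 = 0.0908 and se1 = 0.0847, so (0.36 − 0.178)/0.0847 = 2.149 and power is 98.4%.

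**Effect of carry-forward.** The steroid rate becomes (1 − d)·0.27 + d·e, where d is the share of the steroid arm lost before week 26. The group size stays at 60 because the rule fills every gap.

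| Loss d | Early steroid success e | Steroid rate at month 6 | Difference (points) | Power |
|---|---|---|---|---|
| none | – | 27.0% | 36.0 | 98.4% |
| 5/60 | 50% | 28.92% | 34.08 | 97.1% |
| 5/60 | 70% | 30.58% | 32.42 | 95.4% |
| 5/60 | 90% | 32.25% | 30.75 | 93.1% |
| 20% | 50% | 31.6% | 31.4 | 94.1% |
| 20% | 70% | 35.6% | 27.4 | 86.1% |
| 20% | 90% | 39.6% | 23.4 | 73.3% |

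In patients: with 5 of 60 lost, the rule adds 5·(0.50 − 0.27) = 1.15 to 5·(0.90 − 0.27) = 3.15 steroid successes. With 12 of 60 lost it adds 2.76 to 7.56.

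**Comparison: everyone lost counted as a failure.** At 5/60 loss the rates are 57.75% and 24.75%, a difference of 33.0 points with power 96.5%. At 20% loss they are 50.4% and 21.6%, a difference of 28.8 points with power 91.8%.

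**The case against.** The strongest case for leaving the rule alone has four parts.

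- **Safeguards exist.** Patients known to have had another treatment are already failures, and so are those who needed escape therapy or excess pain medication. This stands, and it narrows the affected group. It does not reach a patient who relapses and simply stops attending.
- **The error is conservative.** On the protocol's own premises the bias favours steroid, so a finding of PRP superiority would not be an artefact of it. This stands for the test. The estimated difference is still wrong.
- **The size is small.** At the planned loss, power stays above the 90% design value throughout the assumed range. This stands. The 20% figure is more than twice the allowance in the article and is only an illustration.
- **The timing is ambiguous.** Recurrence after 6 months could mean relapse later than month 6. But the same paragraph assumes only 27% steroid success at 6 months, and Background and Discussion limit steroid benefit to the short term. Waning by month 6 is the better reading.

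A reader might also infer that PRP patients lost early are frozen before a slower benefit appears, so that the two arms are distorted in opposite directions. The article does not support this. It gives no early PRP success rates, and it lists speed of recovery as something still to be measured. Nor does it support treating every steroid leaver as a carried-forward success and every PRP leaver as a failure. Success still requires the last VAS to show the reduction, and the article calls steroid benefit small.

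The absence of a stated sensitivity analysis is no criticism either, since that may sit in an analysis plan that is not shown.

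**Conclusion.** The point holds in a limited form. The stated rule conflicts with the time course the protocol expects in the steroid arm, and it biases the primary comparison toward steroid. At the planned 5/60 loss the bias is about 2 to 5 points, and power falls from 98% to 97–93%. At an assumed 20% loss it is about 5 to 13 points, and power falls to 94–73%.

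These sizes rest on the assumed 50–90% early steroid success, on PRP unaffected at 63%, and on leavers and completers sharing the same true 6-month rates. They also rest on the 63% and 27% borrowed from tendonitis.

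The rule should be fixed, but at the planned loss it does not by itself undermine the trial.

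**What to change.** Replace the carry-forward sentence for the primary analysis. Impute missing week-26 VAS by multiple imputation within arm, from baseline and the 4-, 8- and 12-week VAS, in all randomised patients, and derive success from the completed values. This also brings in randomised patients with no post-baseline score, whom the present wording leaves unclassified. Keep the stated rule that a patient who obtained a different treatment is unsuccessful.

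Report missing = failure as a sensitivity analysis. It is not neutral: at the planned loss it gives 33.0 points, close to carry-forward with 60% early steroid success (63 − 29.75 = 33.25). It does, however, remove the selective credit to one arm. Keep carry-forward, if at all, as a supportive analysis.

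The cost is one changed paragraph, modest programming and slightly wider confidence intervals. No new data are needed, because VAS is already collected at every visit. The change should be made before unblinding.

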#### Function and quality of life

The function and satisfaction will be measured using the AOFAS foot questionnaire [18,19], the Foot Function Index (FFI) [20-22] and WHOQOL quality of life questionnaire [23,24] questionnaires.

#### Follow up

All patients will be followed up at 4, 8, 12, 26 and 52 weeks. All patients will complete AOFAS and VAS scores at all follow up moments

#### Determination of sample size

This study has two main parameters: number of patients with 25% pain reduction after 6 months and the average pain reduction;

Corticosteroids and stretching have a recurrence of pain after 6 months [2,25]. Previous studies with platelet rich plasma by tendonitis showed that the platelet rich plasma group has no recurrence. These results showed 63 percent success rate (VAS reduction over 25 percent after 6 months) for the platelet rich plasma group compared to 27 percent success rate for the corticosteroid group. If these percentages are comparable for plantar fasciitis 38 patients are needed in all groups to achieve a 25% pain reduction (alfa 0,05 and power 0,9).

Conservative treatment with taping or stretching shows a 30 ± 24 points decrease in VAS pain at walking [26,27]. Corticosteroid injections have shown to have comparable results [2,25]. 25% increase in pain reduction is seen as clinical relevant. To prove a difference in pain reduction of 15 ± 24 points and a α of 0,05 and a power of 0,9, 55 patients are needed in each group.

#### Needed number of patients

To be able to measure a difference in average pain reduction, the largest number of patient is needed 55 patients in both groups. To compensate for possible lost to follow-up, 60 patients will be included in each group (Figure 1).

**Figure 1 F1:**
[figure not shown]
**Flow chart**.

#### Statistical analysis

This is a double blind randomized and prospective study. Patients will be randomized in equal proportions to either autologous platelet concentrate or corticosteroid injections. The primary endpoint of the trial is treatment success at 6 months. The other measurements are to measure the speed of recovery and the re-occurrence of pain.

Statistical analyses will test the null hypotheses of no differences between patients treated with autologous platelet concentrate and those treated with corticosteroid in the proportion of the protocol defined, successfully treated patients.

All tests of treatment effect will be made using a one-sided alpha level of 0.025, unless otherwise specified. Tests for the interaction between treatment and a blocking factor will be made at the alpha level of 0.10. All p-values will be rounded then quoted to 3 decimal places, unless the true p-value is less than 0.001 whereby the notation (p < .001) will be used or if the true p-value is greater than 0.999, in which case the notation (p > .999) will be used. Confidence intervals, where indicated for the difference between the two treatment groups, will be calculated at the 95% level. All data will be analyzed by a blinded researcher.

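### Double blinding is claimed but shown only for the analyst; one person both allocates and monitors, and a single published block length of 10 makes allocation partly predictable to anyone holding past assignments

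*Protocol article*

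**What the plan says.** **Blinding.** The Background announces an evaluation "in a double-blind randomized trial", and the Statistical analysis section repeats: "This is a double blind randomized and prospective study". Neither place says who is blinded. The one party named is in Statistical analysis: "All data will be analyzed by a blinded researcher".

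**Procedures.** Under Platelet Concentrate Preparation, "Fifty-five milliliters whole blood is collected from the uninvolved arm into a 60-mL syringe", followed by centrifugation and buffering; "The total time from blood draw to injection in the patients is about 30 minutes". That section does not limit these steps to the platelet group, and it speaks of concentrate being obtained for every patient. Injection Technique gives the local anaesthetic to both groups explicitly, and then the same stated volume range, needle and peppering technique for either product.

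**Allocation.** Study design states: "A computer using block randomisation of 10 patients will be used to create a randomization schedule". Assignments lie in sequentially numbered opaque envelopes and are assigned, after eligibility and consent, by four trial managers "who will also arrange the facilities needed for the procedure".

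**Monitoring.** Study population names two authors who "will be responsible for the data and safety monitoring". One of them is also among the four trial managers.

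**Endpoint.** Under Main study pain, success requires a 25% reduction in patient-marked VAS pain, no pain medication beyond the permitted period and no escape therapy. A patient who obtains a different treatment is counted as unsuccessful.

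**The concern.** Every part of the success definition can respond to knowledge of the arm: the VAS mark, the use of pain medication and the decision to seek another treatment. The likely direction is also foreseeable, because the Discussion expects the platelet treatment to prove superior. A blinded analyst protects none of these, since they are settled before the data reach the analyst. The patient's blinding therefore matters most, and the article asserts it without showing it.

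Two design facts add to this. The managers hold the assignments and arrange the procedure, and one of them also oversees data and safety, so judgements on data and harms are not independent of knowledge of the arm. And a single published block length removes one protection of the sequence from whoever knows the earlier assignments. If such a person also influences who is enrolled and when, selective enrolment becomes possible.

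**Working it through.** **1. Blinding: the sections set side by side.**

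| Party | What the article says |
|---|---|
| Patient (rates the primary outcome) | Not named as blinded; covered only by the general label |
| Injector | Not named as blinded; handles one of two products |
| Trial managers | Hold the assignments and arrange the procedure |
| Data and safety monitors | One of the two is also a trial manager |
| Analyst | Named as blinded |

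The blood draw and wait can be read in two ways.

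- *Common to both groups.* The wording about every patient supports this. The patient's experience would then be parallel up to and including the injection, and the label could hold for the patient.
- *Platelet group only.* The section heading suggests this, as does the contrast with Injection Technique, which says explicitly that the anaesthetic goes to both groups. A patient could then tell the arm from whether blood was taken.

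The text does not decide between them. On either reading, what the injector can see is not addressed.

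**2. Predictability of a fixed block of 10.** The plan gives no figure of its own for this.

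Inputs: block length 10 (Study design); equal allocation (Statistical analysis), so m = 5 per arm in each block; 60 per group, 120 in total (Needed number of patients), hence 120/10 = 12 complete blocks on a single list.

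Assumption: the guesser knows the block length, where each block starts and every earlier assignment in it.

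- *Allocations known with certainty.* Once one arm is used up, the rest of the block is fixed. The expected number is 2m/(m + 1) = 10/6 = 1.67 of 10, or 16.7%. Over 12 blocks this is 12 × 1.67 = 20 of 120.
- *Best guessing* (always name the arm with more places left; toss a coin on ties). The expected number correct is m + ½[2^(2m)/C(2m, m) − 1] = 5 + ½(1024/252 − 1) = 5 + ½(3.063) = 6.53 of 10, or 65.3%, against 50% by chance.

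Enumerating all 252 orderings of a 5:5 block gives the same two results.

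For comparison, under the same assumption:

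| Fixed block | Certain | Guessed correctly |
|---|---|---|
| 4 | 33.3% | 70.8% |
| 6 | 25.0% | 68.3% |
| 8 | 20.0% | 66.6% |
| 10 | 16.7% | 65.3% |

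If earlier assignments are hidden from the guesser, the gain is nil. The total of 20 assumes one list of complete blocks; the article does not say whether blocks run per hospital or across all four.

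**3. Bias from unblinding.** The document gives nothing from which its size could be derived, so none is offered.

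**The case against.** Three stronger readings are tempting, and the document supports none of them.

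*That the procedures reveal the arm to patient and injector.* A reader might infer this from the section heading over the blood draw. But the draw is not restricted to one group, concentrate is said to be obtained for every patient, and the anaesthetic, volume range, needle, technique and post-procedure regimen are described in common. Nothing is said about how the loaded syringes look or who injects. This is also a condensed article: sleeves, screens and similar masking detail may sit in the full protocol, and their absence here is no error. This part of the objection stands. What survives is that the label is claimed twice, the party that matters most is not named, and the one passage that could settle the matter is ambiguous.

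*That allocations are foreseeable.* The schedule is computer-generated, the envelopes are opaque and numbered, and allocation follows eligibility and consent. The article does not say that managers recruit patients, or that any one of them sees all past assignments across the hospitals. Even with full knowledge, about five of six allocations remain uncertain, and shorter fixed blocks would be worse. This stands too: the exposure is conditional and limited. However, the managers are the people best placed to have that knowledge, and opaque envelopes do not hide past assignments from those who made them.

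*That the shared role breaks the blinding.* Monitoring is neither outcome assessment nor analysis, and the overlap by itself does not reach the patient's VAS mark. It remains a stated lack of independence between allocation and oversight.

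**Conclusion.** The concern holds in a limited form. The article does not establish double blinding beyond the analyst; it also does not show that blinding fails. The overlap between allocation and monitoring is stated outright. The fixed block length is stated too, and its effect is bounded: 1.67 of 10 allocations certain and 65% guessable, only for someone who knows the block boundaries and all earlier assignments in the block. The claim that a double-blind result could not be supported would go too far, because it assumes an unblinding that the text leaves open. This point does not dispute the sample size or the planned test. The changes are worth making because they cost little and the primary endpoint is self-reported.

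**What to change.** 1. For allocations still to be made, generate a new list with randomly varying block sizes, and disclose the sizes to neither sites nor managers. The benefit comes from hiding the boundaries; shorter blocks of known size would be worse than 10.
2. Give data and safety monitoring to a team member with no role in allocation or in arranging the procedure.
3. Reconcile Background, Platelet Concentrate Preparation, Injection Technique and Statistical analysis: state whether the draw and wait are the same in both groups, and name each blinded party (patient, injector, monitor, analyst). If patient or injector is not blinded, replace the double-blind label with a description of what is delivered.

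The cost is a new computer list, one reassigned role, a few sentences and possibly a less favourable blinding label. Nothing here requires an additional blood draw.
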